## Abstract

**Background:**

Infections after elective colorectal surgery remain a significant burden for patients and the healthcare system. Adult studies suggest that the combination of oral antibiotics and mechanical bowel preparation is effective at reducing infections after colorectal surgery. In children, there is limited evidence for either of these practices and the utility of combining oral antibiotics with mechanical bowel preparation remains uncertain.

**Methods:**

This study aims to determine the feasibility of conducting a randomized controlled trial assessing the efficacy of oral antibiotics, with or without mechanical bowel preparation, in reducing the rates of post-operative infection in pediatric colorectal surgery. Participants aged 3 months to 18 years undergoing elective colorectal surgery will be randomized pre-operatively to one of three trial arms: (1) oral antibiotics; (2) oral antibiotics and mechanical bowel preparation; or (3) standard care. Twelve patients will be included in each trial arm. Feasibility outcomes of interest include the rate of participant recruitment, post-randomization exclusions, protocol deviations, adverse events, and missed follow-up appointments. Secondary outcomes include the rate of post-operative surgical site infections, length of hospital stay, time to full enteral feeds, reoperation, readmission, and complications.

**Discussion:**

If the results of this trial prove feasible, a multi-center trial will be completed with sufficient power to evaluate the optimal pre-operative bowel preperation for pediatric patients undergoing elective colorectal surgery.

**Trial registration:**

ClinicalTrials.gov: NCT03593252.

## Background

Colorectal surgery is associated with high rates of surgical site infections (SSI) in both adult and pediatric populations, occurring in up to 25% of all cases [1]. The American College of Surgeons (ACS) National Surgical Quality Improvement Program (NSQIP) pediatric data shows that colorectal procedures account for 2.5% of all pediatric surgical cases but contribute to 7.1% of the SSI burden [2]. Many of the Canadian centers that currently participate in the NSQIP pediatric program, including our hospital, have higher than expected rates of SSIs in elective colorectal cases. This serves as a great impetus to find the optimal SSI reduction strategy for these patients.

Two pre-operative techniques have been proposed as potential methods of reducing infection in colorectal surgery, oral antibiotics (OA) and mechanical bowel preparation (MBP), which aims to cleanse the large bowel of its fecal contents. The evidence is weak for either of these techniques in the pediatric population, and practice patterns remain variable and largely dependent on surgeon preference. A survey conducted by the American Pediatric Surgical Association (APSA) in 2015 showed that the most common approach taken among pediatric surgeons for all intestinal procedures was MBP alone (31.1%), followed by dietary modifications (26.8%), and OA combined with MBP (19.6%) [2]. The current approach at McMaster Children’s Hospital in pediatric patients undergoing a colorectal procedure is intravenous antibiotics with good coverage against gut flora given on induction of anesthesia, without any bowel preparation.

MBP alone has fallen out of favor due to the paucity of beneficial evidence (i.e., clearing the bowel of fecal content does not necessarily reduce the quantity of bacteria in the intestinal mucosa) and the potential increased risk of post-operative complications [3–6]. A Cochrane Review, encompassing 18 randomized controlled trials (RCTs), showed no difference in the rate of wound infection or anastomotic leak in colorectal procedures between patients who underwent MBP and those who did not [4]. More recently, two systematic reviews and meta-analyses support those findings [5, 6]. Lok et al. identified two RCTs and four retrospective cohort studies of patients 0–21 years of age undergoing elective colorectal surgery and assessed the effect of pre-operative MBP on the incidence of post-operative complications including anastomotic leak, wound infection, and intra-abdominal infection [5]. Overall, MBP before colorectal surgery did not decrease the incidence of post-operative infectious outcomes [5]. Similarly, Zwart et al. conducted a meta-analysis on two RCTs and four retrospective comparative studies and found that among patients aged 0–21 years undergoing colorectal surgery, the risk of developing a post-operative infection was 10.1% in patients who received MBP compared to 9.1% in patients who did not receive MBP, resulting in a non-significant risk difference of − 0.03% (95% CI − 0.09 to 0.03%) [6].

With regard to OA alone versus no preparation, the adult literature shows promising results in favor of the use of OA. In a Cochrane Review on antimicrobial prophylaxis in colorectal surgery (*n* = 260 RCTs), the addition of OA to intravenous antibiotics was found to reduce surgical wound infection (RR = 0.56, 95% CI 0.43 to 0.74) [7].

Evaluating a combination approach, a recent network meta-analysis by Toh et al. assessed 8458 adult patients (*n* = 38 RCTs), comparing four bowel preparation groups: (1) OA with MBP; (2) OA only; (3) MBP only; and (4) no preparation [8]. The primary outcome was the total rate of incisional and organ space SSIs. Results showed that MBP with OA was associated with the lowest risk of SSI [8]. The use of OA without MBP was not associated with a significant reduction in SSI [8]. Lastly, there was no difference between MBP only and no preparation [8].

Contrary to the extensive body of research available in adults, there is a noticable gap in studies examining pre-operative bowel preparation for colorectal surgery in children. Moreover, available studies tend to be retrospective in nature with smaller sample sizes. A multi-center, retrospective study by Serrurier et al. assessed outcomes in 272 children who underwent colostomy takedown and found higher rates of wound infection (14% vs 6%, *p* = 0.04) and a longer length of hospital stay among those who received MBP versus no preparation [9]. Another study by Breckler et al. comparing MBP versus OA + MBP in 118 children undergoing colostomy closure for imperforate anus found no difference in SSI rate (13% vs 17%, *p* = 0.64) [10]. In a more recent retrospective cohort study using administrative data, Ares et al. analyzed 1581 pediatric patients undergoing elective colorectal procedures and found post-operative complications to be the highest in the group who received no pre-operative preparation, when compared to those receiving combination preparation (OA + MBP), and MBP alone (23.3%, 15.9%, and 14.2%, respectively; *p* = 0.002) [11]. Interestingly, their findings suggest the addition of OA may be deleterious [11]. Evidence to support the sole use of oral antibiotics opposed to in combination with MBP is lacking, particularly in the pediatric literature.

Due to the existing variability in surgeon preference and the lack of sufficient prospective evidence for either combination OA + MBP or OA alone, we believe that there is a need for a well-designed clinical trial. Before conducting a fully powered multicentre trial, this feasibility study will provide important and pragmatic information on resource requirements, logistics, protocol testing, intervention adherence, and risk assessment.

## Methods

### Study design and objective

This trial design is a parallel, randomized controlled feasibility trial. The trial design is outlined in Fig. 1.

**Fig. 1 Fig1:**
[figure not shown]
Trial design

The primary objective of this trial is to determine the feasibility of conducting a RCT to assess the efficacy of OA, with or without the use of MBP, in reducing the rate of post-operative infections in pediatric patients undergoing elective colorectal surgery and to validate key assumptions for a large-scale superiority trial.

#### Study setting

This study will be conducted at McMaster Children’s Hospital, a pediatric tertiary care teaching hospital located in Hamilton, Ontario, Canada. Pediatric patients undergoing elective colorectal surgery will be screened and recruited from Pediatric General Surgery outpatient clinic.

#### Inclusion criteria

The specific inclusion criteria for this study are the following:Pediatric patients aged 3 months to 18 years being treated by the Pediatric General Surgery service at McMaster Children’s HospitalUndergoing elective colorectal surgeryParents or legal guardians able to give free and informed consentFor females of childbearing age, a negative pregnancy test

These criteria reflect the characteristics of children/adolescents undergoing elective colorectal procedures for which the results will be generalizable. Elective colorectal procedures eligible for this study include (but not limited to) the following:Colostomy closureLarge bowel resection with creation of ostomy or anastomosis/pull-throughTrans-anal pull-throughAnorectoplasty

#### Exclusion criteria

The specific exclusion criteria for this study are the following:Non-elective surgeryProcedures that would not require MBPColorectal resection with an existing proximal diverting ostomyClosure of small bowel ostomyMechanical bowel obstructionKnown hypersensitivity to laxatives (pico-salax and sennaquil) or OA (neomycin and metronidazole)Contraindication to OA Patients on long-term antibiotics (1 month or more) directly before surgeryCongestive heart failureRenal insufficiency (eGFR < 60 ml/min per 1.73 m^2^; Schwartz equation [12])Cockayne syndromePregnant and/or nursingOther medical conditions precluding the use of either OA or MBP Co-enrolment in another intervention trial

#### Interventions

Patients will be randomized to receive either OA + MBP, OA alone, or no preparation (standard of care). If the patient/parents choose not to participate in the trial, the preparation regimen will be at the discretion of the treating surgeon. The trial interventions are detailed in Table 1.

**Table 1 Tab1:** Trial interventions

**Standard care** (all groups)	**Oral antibiotics**	**Mechanical bowel preparation**
• Care according to institutional SSI reduction bundle	Oral non-absorbable antibiotics • Neomycin (15 mg/kg/dose, max of 1 g) To be given the day before surgery at 3 pm, 6 pm, and 9 pm	Two days before surgery No dietary restrictions
		• < 1 year: 5 mL Sennaquil at 4 pm • 1–5 years: 10 mL Sennaquil at 4 pm • > 6 years: 15 mL Sennaquil at 4 pm
	Oral absorbable antibiotics • Metronidazole (15 mg/kg/dose, max of 500 mg) To be given the day before surgery at 3 pm and 9 pm	The day before surgery Light breakfast then clear fluid diet
		• < 1 year: 5 mL Sennaquil at 4 pm • 1–5 years: ¼ sachet Pico-Salax at noon and 4 pm • 6–12 years: ½ sachet Pico-Salax at noon and 4 pm • > 12 years: 1 sachet of Pico-Salax at noon and 4 pm
		The day of surgery
		Care according to standard of care protocol

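### Table 1's bowel preparation age bands disagree at age 6 between the two preparation days, so an eligible child could have no defined first-day laxative dose

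*Protocol article*

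**What the plan says.** Under Interventions, Table 1 lists the laxatives for the oral antibiotics plus mechanical bowel preparation (OA + MBP) arm by day and age.

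- **Two days before surgery:** "< 1 year: 5 mL Sennaquil at 4 pm", then "1–5 years: 10 mL Sennaquil at 4 pm", then "> 6 years: 15 mL Sennaquil at 4 pm".
- **The day before surgery:** the under-1 entry is repeated, followed by "1–5 years: ¼ sachet Pico-Salax at noon and 4 pm", "6–12 years: ½ sachet Pico-Salax at noon and 4 pm" and "> 12 years: 1 sachet of Pico-Salax at noon and 4 pm".

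The Inclusion criteria admit "Pediatric patients aged 3 months to 18 years being treated by the Pediatric General Surgery service", so every age from infancy through adolescence is eligible. The article does not say whether age in Table 1 means completed years or exact age.

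Three other places depend on the regimen in this table. Primary outcome measures counts protocol deviations in terms of compliance with the bowel preparation. The Research Coordinator subsection of Data collection assesses compliance from a family diary of doses and times. Table 2, under Progression criteria, asks that at least 70% of participants complete what was prescribed.

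**The concern.** Two rows of one regimen, for the same children on consecutive days, should divide the eligible ages in compatible ways. These do not: age 6 is named in a band on the second day and excluded by a strict inequality on the first, while the band below stops at 5.

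Two things are at stake. First, this is a paediatric dosing table, and a dose that it leaves undefined for some eligible children bears on safety. Second, a feasibility trial that measures compliance needs a defined regimen to measure against. If Table 1 prescribes nothing for a child on one day, a diary entry showing a dose and one showing none could each be counted as compliant or as a deviation, depending on who classifies it.

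**Working it through.** The plan gives no figure to reproduce; the check is whether the printed bands cover every eligible age.

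**Inputs**
- Eligible ages: 3 months to 18 years, a span of 17.75 years (Inclusion criteria).
- Age bands: Table 1, as quoted above.
- Arm size: 12 (Abstract, Methods: "Twelve patients will be included in each trial arm"; repeated under Sample size).
- Adherence threshold: 70% (Table 2).
- Age convention: not stated, so three readings are tried.
- Age mix of patients: not given, so a range is assumed.

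**Step 1. Coverage.** Every age from 3 to 216 months was compared with the bands for each day.

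| Reading of age | Two days before surgery | Day before surgery |
|---|---|---|
| Completed years throughout | No band for age 6 (72–83 months) | No gap, no overlap |
| Exact age throughout | No band above 5.0 up to and including 6.0 (61–72 months) | No band between 5 and 6 (61–71 months); no overlap |
| Mixed: ranges in completed years, inequalities in exact age | No band on the sixth birthday only (month 72) | No gap; 145–155 months falls in both upper bands |

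**Step 2. Which reading is natural.** Consecutive whole-number bands such as 1–5 and 6–12 meet only if age is in completed years. On that reading the day-before row is complete: 5 is followed by 6, and the top band starts at 13. Applied to the first day, the same reading ends the middle band with the last month of age 5 and starts the top band at 7. The whole of age 6 is left out. Either consistent convention leaves a one-year gap on the first day; only the mixed reading nearly closes it.

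**Step 3. How much of the regimen is undefined.** For a 6-year-old, in completed years, the table would call for three laxative administrations: one of Sennaquil on the first day and two of Pico-Salax on the second. The first is undefined, so 1 of 3.

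**Step 4. How many children.** Let p be the share of patients in the affected one-year band. The expected number in the arm is 12p, and the chance of at least one is 1 − (1 − p)^12.

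| Assumed p | Expected number, 12p | Chance of at least one |
|---|---|---|
| 3% | 0.36 | 1 − 0.97^12 = 31% |
| 5.6% (uniform ages, 1/17.75) | 0.68 | 50% |
| 10% | 1.2 | 1 − 0.90^12 = 72% |

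**Step 5. Effect on the adherence figure.** One child is 1/12 = 8.3 percentage points of the arm. If only that child counted as non-adherent, 11/12 = 91.7% would remain, well above 70%. One classification would change the arm's result only at the margin: 9/12 = 75.0% passes and 8/12 = 66.7% does not. Table 2 does not say that the criterion applies by arm. Pooled over the two arms given an oral regimen, one child is 1/24 = 4.2 points.

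**The case against.** The strongest reply is that this is one symbol in one row, perhaps a slip, or a greater-than-or-equal sign lost when the text was extracted. Loss in extraction cannot be excluded, but it cannot be shown either: the fraction characters in the same table survived, and no such sign appears elsewhere for comparison. If the source shows the same symbol, the conflict is real, and nothing in the article resolves it.

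A second reply is that an article leaves detail to the full protocol and pharmacy instructions. That is right for the definition of age and the date at which it is taken, and their absence is no finding. It does not excuse bands that are printed and conflict with each other. If a fuller document has them right, the published table is still wrong.

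A third reply limits the reach of the point, and it stands. A reader might infer several stronger things that the article does not support:

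- **A two-fold dose ambiguity at age 12** (half against one sachet per dose). This compares two conventions. Under completed years a 12-year-old is in 6–12 and nowhere else, and neither consistent convention produces an overlap.
- **A gap on both days.** This appears only under exact age.
- **Affected children will certainly be enrolled.** No age mix is given, and the chance rests on assumed shares.
- **The pharmacist must improvise.** The Concealment mechanism section has a trained Research Pharmacist prepare and dispense the medication, and the dispensing instructions are not shown.

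**Conclusion.** The point holds as an internal inconsistency in Table 1, confined to age 6 under completed years, or to ages between 5 and 6 under exact age. An eligible child in that year could have no defined first-day dose, and compliance with the prescribed regimen could not then be classified consistently.

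Its size is modest: on the assumed shares, about zero or one child in this arm. By itself it is unlikely to change a progression decision unless adherence is already close to 70%. It deserves correction because it concerns a paediatric dosing rule and a primary outcome, not because it threatens the trial's conclusions.

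The conclusion assumes that the inequality is printed as extracted and that one age convention applies throughout the table. If ranges are read in completed years and inequalities in exact age, the first-day gap shrinks to the sixth birthday, but 12-year-olds past their birthday then fall in two bands on the second day. So none of the three readings gives every eligible age exactly one band on both days.

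**What to change.** The sponsor, with the clinical and pharmacy leads, should reconcile the two rows of Table 1 so that the bands on each day are exhaustive and non-overlapping over the eligible age range, and should confirm that the dispensing instructions carry the same bands. A short note on the age convention (completed years, if that is what is intended) would also remove any doubt at age 12. Which dose or boundary applies is for the sponsor to settle.

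The cost is a correction to one table, plus the dispensing sheet if it repeats the bands. Sample size, randomisation and analysis are unaffected. If children in the affected year have already been treated, the sponsor should record what they were dispensed and set one rule for classifying their compliance before adherence is summarised.

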#### Standard of care

All study patients, regardless of group allocation, will receive institutional standard of care, including utilization of a peri-operative SSI reduction bundle. The components of this bundle (which all patients will be treated according to) are the following:Pre-operative chlorhexidine bath at home the night before surgeryNil per os (NPO) protocol in line with anesthesia requirementsSolids until 8 h before surgeryFormula until 6 h before surgeryBreast milk until 4 h before surgery or clear liquids until 2 h beforeAvoidance of hair shaving before or in the operating roomUse of an alcohol-based skin preparation solution such as chlorhexidine, except for mucosal surfaces (e.g., stoma)On mucosal skin surfaces, use of proviodine solutionAntibiotics given on induction and 1 h or less before incisionCefazolin (30 mg/kg, max 2 g) or metronidazole (15 mg/kg, max 500 mg)In case of allergy to penicillin or cephalosporins, ciprofloxacin (10 mg/kg, max 400 mg/dose) or gentamicin (2.5 mg/kg)Maintenance of normothermia throughout surgerySkin closure with clean instrumentsThe surgery team (surgeons and scrub nurses) change their gowns and gloves and move to a new clean set of instruments at the time of skin closure to minimize contaminationOcclusive dressing applied for 48 h post-operatively

#### Participant timeline

The duration of the treatment period will vary depending on which treatment arm the patient is randomized to. Patients in the OA group will begin treatment 1 day before surgery. Those allocated to the OA + MBP group will begin the study treatments 2 days prior to surgery. All study treatments will be completed prior to surgery commencing.

#### Outcomes

##### Primary outcome measures

The primary outcome measures for this trial will assess the feasibility of conducting a full RCT. The outcomes of interest are the participant recruitment rate (percentage of eligible patients enrolled), the rate of post-randomization exclusions, the number of protocol deviations (compliance to pre-operative bowel preparation regimen), adverse events related to the use of MBP and OA, and missed follow-up appointments.

##### Secondary outcome measures 

The secondary outcomes of interest for this study are the rate of SSIs (both superficial and deep), length of hospital stay, time to full enteral feeds, re-operation (within 30 days of initial surgery), readmission (within 30 days of initial discharge), and complications.

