#### Clinical Outcome Assessor

The Clinical Outcome Assessor will be responsible for collecting data on post-operative infectious complications (superficial and deep SSIs). The SSI will be classified based on the Centres for Disease Control and Prevention definitions [18]. The Clinical Outcome Assessor will be a trained healthcare worker (attending surgeon, surgical fellow, or nurse practitioner) with experience in recognizing infectious complications. They will be responsible for daily patient follow-up in the immediate post-operative period while the patient is admitted to the hospital. They will also conduct the assessment during the follow-up clinic visit after hospital discharge. If a post-operative complication occurs, the mode of treatment will be recorded. If a bacterial culture was obtained, the organism cultured, antibiotics therapy, and duration of antibiotics will be recorded.

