#### Statistical analysis

Demographics will be reported as counts with percentages for categorical variables and means with standard deviations for continuous variables. Feasibility outcome measures (e.g., recruitment rate, post-randomization exclusions, protocol deviations, and adverse events) will be reported as proportions. Secondary outcome measures, such as surgical site infections, re-operation, and complications will be reported as proportions. Length of hospital stay and time to full enteric feeds will be reported as means with standard deviation. In cases where continuous data does not follow a normal distribution, medians with interquartile ranges will be used. The SSI risk ratio and risk difference with 95% CIs will be calculated to estimate the minimum clinically important difference based on clinical data. All data will be analyzed with an intention-to-treat approach using IBM SPSS Statistics Version 25.

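### The SSI outcome is worded as superficial and deep only and never names organ/space infection, so it is unclear whether intra-abdominal infections count

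*Protocol article*

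**What the plan says.** Two sections of the protocol article fix the infection outcome.

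- Secondary outcome measures lists "the rate of SSIs (both superficial and deep" alongside re-operation, readmission and an undefined category of complications.
- Clinical Outcome Assessor makes this blinded role responsible for "collecting data on post-operative infectious complications (superficial and deep SSIs". It adds that "The SSI will be classified based on the Centres for Disease Control and Prevention definitions". The categories of that classification are not listed.

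Three other sections set the context.

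- Study design and objective frames the question as the efficacy of oral antibiotics (OA), with or without mechanical bowel preparation (MBP), "in reducing the rate of post-operative infections in pediatric patients undergoing elective colorectal surgery".
- Background describes the adult network meta-analysis that favours OA with MBP: "The primary outcome was the total rate of incisional and organ space SSIs". It also describes a pediatric review that assessed "post-operative complications including anastomotic leak, wound infection, and intra-abdominal infection".
- Statistical analysis states the use of the outcome: "The SSI risk ratio and risk difference with 95% CIs will be calculated to estimate the minimum clinically important difference".

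**The concern.** The outcome is worded more narrowly than the question. The question covers post-operative infection without restriction to the wound. The outcome and the assessor's task name two depths of infection, and neither names the organ/space level. The Background shows that the authors know organ space as a category distinct from incisional infection.

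At stake is how an intra-abdominal abscess or an infected anastomotic leak is coded when the wound itself is clean. If it is not an SSI, it is absent from the SSI rate and from both effect measures, and it appears only among complications. These events are plausible here, because the eligible operations include large bowel resection with anastomosis and pull-through procedures. A feasibility trial is also the place to test an outcome definition before a larger trial adopts it.

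**Working it through.** The article states no figure that depends on this definition, so there is none to reproduce. The check is a comparison of sections, followed by one line of arithmetic on size.

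**1. Wording of the outcome.** Secondary outcome measures names superficial and deep. Clinical Outcome Assessor repeats the pair as "post-operative infectious complications (superficial and deep SSIs", where the parenthesis spells out infectious complications as those two levels. The sections on outcomes, data collection and statistical analysis contain no mention of organ/space infection, intra-abdominal infection or anastomotic leak.

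**2. Wording of the question and of the evidence.** The objective says post-operative infections. The network meta-analysis counted incisional plus organ space SSIs. The pediatric review listed intra-abdominal infection separately from wound infection. The article's own vocabulary therefore has an organ/space category that its outcome does not name.

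**3. One patient under each reading.** Take a patient with an intra-abdominal abscess and a clean wound.

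- Literal reading: neither superficial nor deep, so not an SSI. The event is recorded as a complication and is absent from the SSI rate, risk ratio and risk difference.
- Inclusive reading, with deep covering everything below the superficial layer or the cited classification supplying the category: the event is an SSI and enters all three.

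Nothing in the article decides between the two readings, so two assessors could code the same patient differently.

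**4. Who classifies it.** The Clinical Outcome Assessor is blinded (Blinding). The Research Coordinator is not blinded and collects adverse events (Blinding; Research Coordinator). Families who suspect an infection after surgery are referred to the assessor for confirmation, so many such events would reach a blinded person. What is unassigned is the classification of an infection that is neither superficial nor deep.

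**5. Size.** The input is 12 patients per arm (Sample size). One patient moved into or out of the SSI count changes that arm's rate by 1/12 = 0.083, or 8.3 percentage points. It changes any risk difference involving that arm by the same amount. This holds only for a patient with no incisional SSI as well, because a patient with both is counted either way. The article gives no organ/space share, so the expected number of such patients cannot be derived from it.

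**The case against.** The strongest reply is that nothing is expressly excluded. The paired wording can be an inclusive shorthand, and the classification is delegated to a named standard. A journal article may reasonably leave form categories to the full protocol. This stands in part. It rules out saying that organ/space infection has been left out, and supports only that it is not named. It does not remove the point, because the narrower list appears in both places that define and operationalise the outcome.

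A second reply is that the data would not be lost. Complications, re-operation and readmission are collected, and the assessor records the treatment of complications and any culture results. An abscess could probably be recoded later. That is true, but the planned SSI estimates would omit it unless someone decided to recode, and the article provides for no such step.

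A third reply is that SSI is a secondary outcome in 36 patients. An observed 2 of 12 has an exact 95% interval of roughly 2% to 48%, so random error dwarfs the effect of the definition. This is correct and limits the weight of the point. An unclear definition is nevertheless a separate fault from imprecision, and a larger trial that inherited the wording would inherit the ambiguity.

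Three stronger readings may tempt a reader, and the article does not support them.

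- That the outcome cannot be compared with the cited evidence in general. The other adult review, on adding OA, is quoted for surgical wound infection. One pediatric cohort is quoted for wound infection, and the Discussion opens on wound infections. The mismatch is with the network meta-analysis and the pediatric review quoted above.
- That this trial supplies the main trial's baseline event rate. The article speaks of checking key assumptions and of using the risk ratio and risk difference to estimate a minimum clinically important difference. It does not say where the main trial's control rate will come from, and it does not name that trial's primary endpoint.
- That the main trial's sample size would be wrong by a calculable amount. This would need an organ/space share, a control rate and a target effect for planning, none of which the article fixes. If the main trial kept the same definition, its planned size would fit that definition.

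**Conclusion.** The point holds as an unclear and, read literally, too narrow outcome definition. The article words both the SSI outcome and the blinded assessor's infection task as superficial and deep. Its question is broader, and the network meta-analysis cited for the combination arm counted organ space infection. On the literal reading, intra-abdominal infections are missing from the SSI rate, risk ratio and risk difference.

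The consequence is confined to this secondary outcome and to what is carried forward from it. The primary feasibility outcomes, the progression criteria in Table 2 and the choice of 12 per group do not depend on it. The number of patients who would be misplaced is unknown, and no main-trial sample size should be attached to the point. The conclusion assumes that the full protocol or case report form does not already name the organ/space level. If it does, the article's wording need only be brought into line.

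**What to change.** In Secondary outcome measures and in Clinical Outcome Assessor, define SSI as superficial incisional, deep incisional or organ/space infection, with all three levels classified by the blinded assessor under the classification already cited. In Statistical analysis, report each level and the composite of any SSI, and state that the risk ratio and risk difference refer to the composite.

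If the investigators do intend incisional infection only, they should say so in both places, give the reason, and describe the objective accordingly.

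The cost is a wording change and one additional category on the case report form. The assessor already sees these patients daily in hospital and at the clinic visit, so no visit, test or patient is added.
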